### Statistical analyses

Continuous variables following a normal distribution will be expressed as mean ± standard deviation; asymmetrically distributed continuous variables will be expressed as median and interquartile range; and categorical variables will be expressed as absolute and relative frequencies. For between-group comparisons, Student’s *t-*test will be used for normally distributed variables, and the Mann–Whitney *U* test for asymmetrically distributed variables. A paired *t*-test will be used for within-group analysis of body weight and congestion score. The chi-square or Fisher’s exact tests will be used to evaluate associations between categorical variables. The generalized estimating equations test with Bonferroni adjustment will be used for comparison between variables during the study period. The significance level will be set at 5%, and all data will be analyzed in SPSS 18.0 (SPSS Inc., Chicago, IL, USA).

For assessment of clinical stability, in accordance with pre-established criteria, two blinded examiners (physician HF specialists not involved in the care of the study participants) will analyze the outcome variables in both groups.

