### Sample size

Sample size calculations were carried out in WINPEPI 11.20 (Brixton Health, Israel). We used the weight loss values reported in the studies of Aliti and colleagues [25] and Cardoso and colleagues [27], which assessed weight loss in patients with HF and systolic dysfunction admitted for HF decompensation and congestion. For a significance level of α = 0.05 and a statistical power of 80%, with a standard deviation of 3 kg and a between-group difference in weight corresponding to a weight loss of 2 kg in 7 days, the minimum sample size will be 74 patients (37 randomized to each group).

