### Study protocol

Patients who meet the inclusion criteria and are eligible will be invited to take part in this trial during their hospitalization. Data will be collected on sociodemographic parameters, clinical variables, results of laboratory tests performed as part of routine patient care (creatinine, urea, potassium, sodium, complete blood count, and BNP on admission), current medications, body weight, and clinical congestion score, and blood will be collected for assessment of neurohormonal activation. Patients will then be randomized to IG or CG.

Once allocation has been completed, the on-call dietitian will be notified so as to change the participants’ meal plan as appropriate. The same dietary prescription will be used for participants in both the IG and CG: *DIET AS PER RESEARCH PROTOCOL. PATIENT WILL RECEIVE DIET UNTIL __/__ OR DISCHARGE. PLEASE DO NOT ALTER DIET.* This practice will be implemented in agreement with the medical staff and with the hospital Department of Nutrition and Dietetics.

A daily check of medical records will be performed to identify modification of any drug prescription. The search for hypotensive episodes will be performed by checking blood pressure every 6 hours and by questioning patients about symptoms of hypotension (dizziness, fainting or lightheadedness) on a daily basis.

Outcomes assessment 30 days after discharge will be carried out at the study facility by means of a face-to-face encounter between the investigators and each participant, at which time a clinical assessment will be performed and blood will be collected for analysis of neurohormonal activation (Figure 1).

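### The primary test is left to the observed distribution; one permitted branch does not target the 2 kg mean difference behind the sample size, and no baseline covariate is planned

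*Protocol article*

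**What the plan says.** The Primary outcome section of the protocol article makes weight loss at 7 days or discharge the primary measure. The Sample size section plans for "a between-group difference in weight corresponding to a weight loss of 2 kg in 7 days", "with a standard deviation of 3 kg", and concludes that "the minimum sample size will be 74 patients (37 randomized to each group").

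The Statistical analyses section gives no analysis specific to that outcome. It has a general rule for between-group comparisons: Student's t-test "will be used for normally distributed variables, and the Mann–Whitney" test for asymmetric variables. Asymmetric variables are to be described by median and interquartile range. The section states no criterion for calling a variable normal. It adds paired t-tests within groups for body weight and congestion score, and generalized estimating equations (GEE) for comparisons over the study period, tied to no named outcome. No between-group comparison names a baseline covariate.

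The Study protocol section lists the data taken before randomization. They include "current medications, body weight, and clinical congestion score".

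**The concern.** The primary test is decided by how the weight-loss data look, and the two candidates answer different questions. The t-test compares means, in kg. The Mann–Whitney test asks whether values in one arm tend to exceed those in the other. It coincides with a test of means only if the two distributions differ by a pure shift.

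A restricted diet against an unrestricted one could change the spread or skewness of weight loss as well as its centre. If so, a significant rank test need not mean a difference in mean weight loss. Under the descriptive rule the result might then be reported as medians, with no mean difference in kg to set against the 2 kg planned.

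The second part is precision. With 37 per arm, simple randomization and no stratification described, the arms may differ by chance in starting weight or congestion. Covariate adjustment accounts for this, and it needs nothing beyond what is already recorded.

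**Working it through.** **Inputs.** From Sample size: alpha 0.05, power 80%, SD 3 kg, difference 2 kg, 37 per arm. Sidedness is not stated. Two-sided is assumed because it reproduces the stated size; one-sided gives 28 per arm and does not. Assumed, because the article gives no value: the joint (multiple) correlation *r* of the baseline covariates with weight loss, shown from 0 to 0.5.

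**1. The plan's own figure.** Normal approximation: n per arm = 2 × [3 × (1.96 + 0.84) / 2]² ≈ 35.3, so 36 per arm (72). The exact two-sample t calculation gives 36.3, so 37 per arm (74), which matches. Power of the unadjusted t-test at 37 per arm is 80.8%. This is a sample size for a difference in means.

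**2. Baseline-adjusted linear model.** Residual SD = 3 × √(1 − r²). Standard error of the group difference = residual SD × √(2/37). Power comes from the noncentral t distribution with 71 degrees of freedom. A second covariate costs one more degree of freedom and changes power by about 0.02 percentage points or less.

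| r (assumed) | Residual SD, kg | Power at 37 per arm | n per arm for 80% |
|---|---|---|---|
| 0 | 3.000 | 80.7% | 37 |
| 0.1 | 2.985 | 81.1% | 36 |
| 0.2 | 2.939 | 82.3% | 35 |
| 0.3 | 2.862 | 84.3% | 34 |
| 0.4 | 2.750 | 87.0% | 31 |
| 0.5 | 2.598 | 90.4% | 28 |

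**3. Mann–Whitney on normal data.** With relative efficiency 0.955, the effective n is 37 × 0.955 = 35.3 per arm, and power is 78.9%.

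**4. The two-stage rule, same shape in both arms.** Simulation with 10,000 trials per scenario, 37 per arm, r = 0.3. The article states no normality criterion, so one was assumed: Mann–Whitney if Shapiro–Wilk gave p < 0.05 in either arm, otherwise the t-test.

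| Shape | Mann–Whitney chosen | Type I error, two-stage | Power, two-stage | Power, linear model |
|---|---|---|---|---|
| Normal | about 10% | 4.7% | 80.8% | 83.9% |
| Mild skew | about 65% | 5.4% | 83.7% | 83.9% |
| Strong skew (two shapes) | about 94% | 5.3%, 5.0% | 90.4%, 93.4% | 83.5%, 84.0% |
| Heavy tails | about 55% | 4.9% | 87.6% | 83.6% |

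**5. The two-stage rule, equal means but different shape or spread.** Normal against skewed, both SD 3: rejection in 8.1% of trials (t-test 5.4%). Both skewed, SD 2 against 4: rejection in 20.4% (t-test 5.5%). A repeat simulation of equal means with different shape or spread gave about 9% to 22%, with the t-test at about 6%. These shapes are illustrations, not estimates from this trial.

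**The case against.** The strongest case against is that this is a condensed article. A normality criterion, a covariate list and the full primary model are often left to the full protocol or analysis plan, and an unadjusted comparison is valid in a randomized trial. This stands as far as it goes: the missing covariates alone would be a matter of preference. The distribution-dependent choice of test is different, because the article states it outright.

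Five stronger readings are tempting, and the article does not support them:

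- *Adjustment is always more powerful.* It is not. At r = 0 there is no gain, at 0.2 about 1.5 points, and with strong skew or heavy tails the two-stage rule had more power than the linear model.
- *The plan ignores baseline data.* Weight loss is already a change from baseline weight. What is absent is covariate adjustment.
- *The rule inflates type I error in general.* With the same shape in both arms it stayed between 4.7% and 5.4%. The excess appears only when shape or spread differs.
- *The GEE is a competing primary test.* The article does not assign it to weight loss. It fits the repeated hormone and thirst measurements equally well.
- *Chance imbalance biases the unadjusted estimate.* Over repeated randomizations it does not, and the standard error already allows for it. Adjustment is for precision and for the estimate in the one trial actually run.

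**Conclusion.** The concern holds in a limited form. The article lets the data choose the primary test, and one of the two branches neither tests nor estimates the mean difference that the trial was sized on. The t-test branch does. The consequence can be small: with normal data, the rule behaves almost exactly like the t-test. It matters if the arms differ in shape or spread, where rejection with equal means reached about 8% to 22% in the simulated examples.

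The gain from adjustment is conditional, from none to about 10 points of power for r between 0 and 0.5. That range is an assumption, as are the two-sided test, the planned SD of 3 kg and the normality criterion used in simulation. The sample size of 74 is correct and is not affected. The change is worth making because it fixes the question being answered at almost no cost; a guaranteed gain in power is not the reason.

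**What to change.** Name one primary analysis in the plan: a linear model (ANCOVA) of weight change at day 7 or discharge on group, with baseline weight and baseline congestion score as covariates. Report the adjusted mean difference in kg with a 95% confidence interval and robust standard errors, whatever the distribution looks like. Keep the unadjusted t-test and the Mann–Whitney test as sensitivity analyses, and state which outcomes the GEE serves.

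Before the congestion score is used as a covariate, settle its definition: the Clinical congestion score section speaks of seven questions but lists eight items.

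The cost is a change of wording. Both covariates are already collected before randomization, the sample size stays at 74, and the Trial status section reports only thirteen completed patients, so the choice could be fixed before the outcome data are analysed. The downside to accept is that with strongly skewed or heavy-tailed weight loss the linear model may have less power than the rank test: about 84% against 90% to 93% in the strongly skewed examples.

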In an attempt to bridge the knowledge gap in patients with decompensated HF-PEF, this trial seeks to compare the effect of a sodium- and fluid-restricted diet versus an unrestricted diet on weight loss, neurohormonal activation, and clinical stability at 7 days or at hospital discharge in patients admitted for decompensation of HF-PEF.

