### Primary outcome

The primary outcome measure shall consist of weight loss at 7 days or discharge.

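### The paired t-tests within each arm on body weight and congestion score say nothing about the diet contrast; a baseline-adjusted between-arm comparison should carry the conclusions.

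*Protocol article*

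**What the plan says.** - **Within-arm tests.** The Statistical analyses section says that a paired t-"test will be used for within-group analysis of body weight and congestion score". This is the only sentence of that section that names either variable, and nothing in it marks the tests as descriptive. One general rule covers all tests: "The significance level will be set at 5" per cent.
- **Between-arm tests.** The preceding sentence is generic. For comparisons between groups, Student's t-"test will be used for normally distributed variables", with Mann–Whitney U for skewed ones. A later sentence adds GEE with Bonferroni adjustment over the study period, again without naming a variable.
- **Aim.** The Background sets out to "compare the effect of a sodium- and fluid-restricted diet versus an unrestricted diet on weight loss".
- **Primary outcome.** "The primary outcome measure shall consist of weight loss at 7 days or discharge".
- **Sample size.** The calculation is framed "with a standard deviation of 3 kg and a between-group difference in weight corresponding to a weight loss of 2 kg in 7 days", and concludes that "the minimum sample size will be 74 patients (37 randomized to each group").
- **Baseline data.** Under Study protocol, body weight and the congestion score are both recorded before randomisation.

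**The concern.** The randomised question is whether the two diets differ. A paired test asks whether the patients in one arm changed. Patients enter shortly after admission for decompensated heart failure with signs of congestion, so loss of weight under ordinary care is plausible in both arms, whatever the diet.

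Two misreadings could follow, and they belong to different situations:

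- If the common loss is large, both arms are significant, and the change in the restricted arm may be credited to the diet.
- If the common loss is small, one arm may be significant and the other not, and this may be taken for a difference between diets.

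In both cases the p-value that names body weight would not be the p-value that answers the trial's question.

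**Working it through.** **Inputs from the protocol article:** SD 3 kg; difference 2 kg; α 0.05; power 80%; 37 per arm (Sample size).

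**Assumptions:** tests are two-sided (sidedness is not stated); the 3 kg is the SD of weight change; changes are roughly normal and the arms independent; all 37 per arm are analysed. The article gives no weight loss common to both arms, so a range of 0 to 4 kg is used.

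**Step 1. Reproduce the plan's figure.** The normal approximation gives

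n per arm = 2(1.960 + 0.842)² × 3² / 2² = 35.3, rounded up to 36 (72 in total).

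Exact power of the two-sample t-test is 79.7% at 36 per arm and 80.8% at 37. The t-based answer is therefore 37 per arm, 74 in total, as stated. A one-sided test would need only 28 per arm. The trial is thus sized for a two-sided comparison between arms.

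**Step 2. The paired test in one arm.** The standard error of the mean change is 3/√37 = 0.493 kg, and the two-sided 5% critical value on 36 degrees of freedom is 2.03. For a true loss m, the noncentrality is m/0.493: 2.03 at 1 kg and 4.06 at 2 kg. The noncentral t distribution gives p, the chance of significance in one arm.

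**Step 3. Both arms, no diet effect.** With the same loss m in each arm, both are significant with probability p², and exactly one with probability 2p(1 − p).

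| Common loss (assumed) | p, a given arm | Both arms | Exactly one arm |
|---|---|---|---|
| 0 kg | 5.0% | 0.3% | 9.5% |
| 0.5 kg | 16.7% | 2.8% | 27.8% |
| 1 kg | 50.5% | 25.5% | 50.0% |
| 1.5 kg | 84.1% | 70.8% | 26.7% |
| 2 kg | 97.6% | 95.3% | 4.6% |
| 3 kg | over 99.9% | over 99.9% | 0.01% |
| 4 kg | over 99.9% | over 99.9% | practically 0 |

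By symmetry, half of the last column is the case in which only the restricted arm is significant: 0.505 × 0.495 = 25% at 1 kg.

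The between-arm t-test keeps its 5% error rate in every row, because the common loss cancels.

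**Step 4. A real diet effect of the planned size.** Let the control arm lose 2 kg and the restricted arm 4 kg. The paired tests are significant with probability 97.6% and over 99.9%, so both are significant about 97.6% of the time. With no diet effect and a common loss of 2 kg, both are significant 95.3% of the time. The pair of verdicts hardly distinguishes the two situations. The between-arm test separates them, with 5% significance against 80.8%.

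**Step 5. Gain from baseline adjustment.** Adjusting the comparison of weight change for baseline weight multiplies the residual variance by about 1 − r², where r is the within-arm correlation of baseline weight with the change. The article gives no r, so no figure is put on the gain. If r is near zero, the cost is one degree of freedom.

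The figures above are for weight only. The article gives no SD for the congestion score, but the reasoning is the same.

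**The case against.** The strongest reply is that the plan already contains the right tests. The sentence before the paired t-tests provides for comparisons between groups, and weight loss, as a continuous variable, falls under it. GEE is planned as well. The paired tests are called within-group, and the aim and the sample size are framed between groups. All of this stands.

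A reader might therefore infer too much in three ways:

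- **That the primary outcome will be judged by paired tests.** No section says so. The article also does not designate one test for weight loss, but a condensed article may leave that to a fuller plan, so it is no finding here.
- **That both misreadings threaten at full size together.** They do not. At a common loss of 4 kg, t = 4/0.493 = 8.1 in each arm and discordance is practically nil. The 50% needs a loss of about 1 kg, and at 2 kg discordance is already down to 4.6%.
- **That the article shows both arms will improve.** It does not; this is an inference from the population. The point survives without it: at zero change, exactly one arm is still significant 9.5% of the time.

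It is also fair to say that relabelling alone does little. A 95% confidence interval for the per-arm change that excludes zero is the same decision as the paired test at 5%. The useful part of the change is to tie the conclusions to an adjusted between-arm estimate.

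**Conclusion.** The point holds as an improvement that costs nothing. The only tests tied by name to body weight and congestion score are within-arm tests, and their verdicts carry practically no information on the diet contrast. Given 37 per arm, an SD of change of 3 kg and no diet effect, a given arm is significant about 50% of the time at a common loss of 1 kg and 98% at 2 kg; exactly one arm is significant about 50% and 5% of the time respectively. These figures rest on the assumed common loss and on reading the stated SD as that of weight change. What is at risk is the interpretation of the results: the planned between-arm t-test keeps its error rate and has 80.8% power for 2 kg.

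**What to change.** In the Statistical analyses section:

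1. Drop the paired t-tests, or label them descriptive and report the mean change with its 95% confidence interval in each arm, without p-values.
2. Analyse weight and congestion score between arms with a model that includes the arm and the baseline value of the same variable, and report the adjusted difference with its 95% confidence interval.
3. State that conclusions about the diet rest on that between-arm difference only, and not on a comparison of significance across arms.

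The cost is a few sentences of analysis wording. The baseline values are already collected before randomisation, so data collection does not change, and the target stays at 74 patients. The article reports that recruitment is continuing, with thirteen patients having completed the protocol.

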## Discussion

During protocol, patients will receive the standard hospital diet for both the control (normal diet) and intervention group (low-sodium diet), modified only in the amount of fluid offered to the intervention group. During the study, patients will be instructed to consume only foods and beverages offered by the hospital. The plate-waste method shall be used to measure sodium intake for 7 days or until hospital discharge, whichever comes first. A trained investigator will assess dietary intake twice daily: after lunch, for collection of information on intake during breakfast, morning snack, and lunch; and after dinner, for collection of information on intake during the afternoon snack, dinner, and supper. In addition, a visual scale (with values ranging from 0 to 10) will be used to verify the degree of thirst.

## Trial status

The trial is ongoing. Thirteen patients have completed the study protocol and additional patients are being recruited.

## Abbreviations

BNP: B-type natriuretic peptide
CG: control group
HF: heart failure
HF-PEF: heart failure with preserved ejection fraction
IG: intervention group
